## Abstract

**Background:**

Malnutrition is very common in patients undergoing cardiac surgery. Malnutrition can change myocardial substrate utilization which can induce adverse effects on myocardial metabolism and function. We aim to investigate the hypothesis that there is a disturbed amino acids profile in the cardiac surgical patient which can be normalized by (par)enteral nutrition before, during and after surgery, subsequently improving cardiomyocyte structure, cardiac perfusion and glucose metabolism.

**Methods/Design:**

This randomized controlled intervention study investigates the effect of uninterrupted perioperative (par)enteral nutrition on cardiac function in 48 patients undergoing coronary artery bypass grafting. Patients are given enteral nutrition (n = 16) or parenteral nutrition (n = 16), at least two days before, during, and two days after coronary artery bypass grafting, or are treated according to the standard guidelines (control) (n = 16). We will illustrate the effect of (par)enteral nutrition on differences in concentrations of amino acids and asymmetric dimethylarginine and in activity of dimethylarginine dimethylaminohydrolase and arginase in cardiac tissue and blood plasma. In addition, cardiomyocyte structure by histological, immuno-histochemical and ultrastructural analysis will be compared between the (par)enteral and control group. Furthermore, differences in cardiac perfusion and global left ventricular function and glucose metabolism, and their changes after coronary artery bypass grafting are evaluated by electrocardiography-gated myocardial perfusion scintigraphy and ^18^F-fluorodeoxy-glucose positron emission tomography respectively. Finally, fat free mass is measured before and after intervention with bioelectrical impedance spectrometry in order to evaluate nutritional status.

**Trial registration:**

Netherlands Trial Register (NTR): NTR2183

## Background

Malnutrition is very common in patients undergoing cardiac surgery as well as other types of surgery. For example, in a population of cardiac and abdominal surgical patients, respectively 10-25% [1,2] and 44% [3] was malnourished. Malnutrition is an independent risk factor resulting in more complications, and increased mortality rates, length of hospital stay and costs [1-3]. The lack of optimal nutrition can change myocardial substrate utilization which can have adverse effects on myocardial metabolism such as adenosine triphosphate (ATP) production and utilization [4]. For that reason, malnutrition might be an underlying risk factor for the perioperative cardiac complications observed in patients undergoing non-cardiac surgery [5]. In addition to cardiac complications, the lack of optimal nutrition can induce nutrient deficiencies which in turn can lead to the impairment of the immune system [6]. It is still common practice that patients receive only clear fluids during the period prior to surgery and the day after surgery leading to starvation of the patient over a longer period of time. As this occurs, glycogen reserves that last only a few hours will deplete with the result that further fasting induces gluconeogenesis. As this gluconeogenesis mainly depends on catabolism of body proteins it furthers the negative effects of malnutrition. We hypothesize that avoidance of malnutrition and starvation can improve cardiac metabolism and function, and might prevent protein catabolism, which would be beneficial for both cardiac and non-cardiac surgical patients.

Nitric oxide (NO), created from the amino acid arginine, is a regulator of cardiac and vascular function. However, the actions of NO can be disturbed by elevated levels of the NO synthase (NOS) inhibitor, asymmetric dimethylarginine (ADMA), a condition reported in patients with failing hearts [7]. Moreover, ADMA has been indicated as marker of circulatory function and as predictor of outcome in patients with cardiac dysfunction [7,8]. As NO availability might be reflected by the ratio between substrate (arginine) and inhibitor (ADMA), the negative effects of ADMA might be relieved by supplementation of arginine. However, the effect of arginine supplementation is complicated as studies have shown both positive and negative results in critically ill patients [7]. Probably, the ratio between arginine and ADMA might play a role as NO availability needs to be perfectly balanced in order to guarantee proper cardiac contraction and vascular dynamics. We hypothesize that nutrition containing arginine is a safe method that might improve the whole amino acid profile in patients with cardiac dysfunction.

Therefore, in this proof-of-concept study, we aim:

(1) To evaluate the effect of uninterrupted perioperative (par)enteral nutrition supplementation versus no supplementation on amino acid profile and cardiomyocytes structure in patients undergoing coronary artery bypass grafting (CABG).

(2) To study the effect of uninterrupted perioperative (par)enteral nutrition supplementation versus no supplementation on myocardial perfusion, left ventricle function and glucose metabolism before and after CABG.

(3) To study the effect of uninterrupted perioperative (par)enteral nutrition supplementation versus no supplementation on fat free mass (FFM, as a marker of nutritional status) before and after CABG.

## Methods/Design

### Design

This is a randomized controlled intervention study. The research protocol of this clinical trial (NTR2183, EudraCTnr 2009-017812-33) has been reviewed and approved by the Medical Ethical Committee of the Academic Medical Center of the University of Amsterdam (AMC) (MEC 09/304) and the Competent Authority of the Netherlands (Centrale Commissie Mensgebonden Onderzoek) (NL28231.018.09).

### Participants

Patients undergoing cardiac bypass surgery are selected to study the effects of (par)enteral nutrition on human cardiac tissue. In order to prevent cardioplegic effects on cardiomyocytes, selected patients are undergoing an off-pump CABG-procedure. Forty-eight patients with stable anginal complaints planned for an elective CABG who meet all inclusion criteria and do not have any of the exclusion criteria (Table 1) will be randomized by computer-generated block randomization (each block including six patients) to one of the three study groups.

**Table 1 T1:** Inclusion & exclusion criteria

Inclusion criteria:	
	•Undergoing off-pump CABG-surgery
	•Age 18 till 80 years
Exclusion criteria:	
	•Combined valve and CABG procedure
	•Age <18 and ≥ 80 years
	•Diabetes mellitus type I
	•Pregnancy
	•Renal insufficiency defined as creatinine > 95 μmol/L for women and > 110 μmol/L for men
	•Liver insufficiency defined as ALAT > 34 U/I for women and > 45 U/I for men

ALAT, alanine aminotransferase; CABG, coronary artery bypass grafting;.

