### Setting

Figure 1 depicts a flow chart of the study protocol. The study is currently performed at the department of cardio-thoracic surgery of the AMC. Patients are informed about the study by a cardiologist and nutritionist who hand over the information letter as well as the informed consent form. A patient is included in the study when the informed consent form is signed. Subsequently, the patient can be randomized to one of the three groups: the "enteral group" (n = 16), the "parenteral group" (n = 16), or the control group (n = 16). During visits at the hospital outpatient clinic (approximately two weeks before surgery), patients are subjected to baseline measurements including blood sampling, measurement of body weight and height, bioelectrical impedance spectrometry (BIS), ECG-gated myocardial perfusion scintigraphy (MPS) and a ^18^F-fluorodeoxy-glucose positron emission tomography (^18^F-FDG PET) scan (Table 2). As part of the preoperative evaluation, patients will also undergo preoperative assessments by a cardiothoracic surgeon and an anesthesiologist.

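### One published block size of six, in a single-department trial with visibly different arms, lets recruiters deduce up to a fifth of allocations if they know all earlier ones

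*Protocol article*

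**What the plan says.** The Participants section gives the sample as "Forty-eight patients with stable anginal complaints planned for an elective CABG" and states that they "will be randomized by computer-generated block randomization (each block including six patients) to one of the three study groups". One size is given for every block. The Setting section lists three groups of 16 and describes a single site: "The study is currently performed at the department of cardio-thoracic surgery of the AMC". No stratification is described.

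On recruitment, the Setting section says: "Patients are informed about the study by a cardiologist and nutritionist who hand over the information letter as well as the informed consent form". On order, it says: "A patient is included in the study when the informed consent form is signed. Subsequently, the patient can be randomized". Table 2 puts consent, randomisation and all baseline measurements in the same day -14 column.

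The arms differ in ways that staff can see. According to Table 2 and the nutrition sections, enteral patients take a drink at home from day -7 and later have a nasoduodenal tube, parenteral patients receive an infusion, and controls have neither. The two nutrition arms are admitted three days before surgery and controls one day before. The only blinding stated, at the end of the section on tissue pathological evaluation, is that of the analysts.

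**The concern.** When the block size is constant and known, the later places in a block can be deduced from the earlier ones. Hiding the list in envelopes or a central system does not prevent this, because the deduction uses only the block size and the allocations already made. Here the size is in print during recruitment, there is one apparent sequence to follow, and past allocations become visible on the ward.

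A recruiter who can anticipate the next arm can bring a patient forward, hold one back or decide not to approach one, for example to keep a frail patient out of a tube-feeding arm. With 16 patients per arm there is little to dilute such choices. Blinded reading of samples and images protects assessment, but it cannot undo selection at entry.

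**Working it through.** **Inputs.** Block size 6 and total 48 (Participants); three groups of 16 (Setting). The article does not state the composition of a block. Two patients per arm is inferred.

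**The plan's own figures.** 48 / 6 = 8 complete blocks, and 8 × 2 = 16 per arm. This reproduces the stated group sizes, so 2:2:2 is the natural reading.

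**Full knowledge of earlier allocations.** A 2:2:2 block has 6!/(2!·2!·2!) = 90 equally likely sequences, all of which were enumerated.

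- *Certain allocations* (only one arm left): probability 0 at positions 1 to 4, 1/5 at position 5 and 1 at position 6. The sum is 1.2 per block, so 1.2 / 6 = 20% and 8 × 1.2 = 9.6 of 48. At least 8 are certain in every realisation, namely the last of each block.
- *Control no longer possible*: after k earlier allocations the probability is C(k,2)/C(6,2). Over positions 1 to 6 this gives 0 + 0 + 1/15 + 3/15 + 6/15 + 10/15 = 20/15 = 1.33 per block, or 10.7 of 48 (22%).
- *Best guess* (the arm with most places left): 1/3 + 2/5 + 1/2 + 8/15 + 3/5 + 1 = 3.367 correct per block. 3.367 / 6 = 56.1%, against 33.3% by chance.

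**Delayed knowledge.** The visible cues begin at day -7 (home drink), day -3 (admission of the nutrition arms) and day -1 (admission of controls), all after randomisation at day -14. The enumeration was therefore repeated with the latest allocations unknown to the recruiter.

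| Latest allocations unknown | Certain, of 48 | At least one arm ruled out | Best guess right |
|---|---|---|---|
| 0 | 9.6 (20%) | 46.7% | 56.1% |
| 1 | 1.6 (3.3%) | 30.0% | 45.0% |
| 2 | 0 | 13.3% | 40.6% |

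With one unknown, only position 6 can be certain, and only when the two remaining places belong to the same arm (probability 1/5): 8 × 0.2 = 1.6. With two unknown, three places always remain at position 6 and an arm has at most two, so nothing is certain.

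**Effect of varying the block size.** In simulated sequences of 48, the recruiter was assumed to know every earlier allocation and the menu of possible sizes, but not the size of the current block. The share of certain allocations was about 8.6% for sizes 3 and 6, 5.0% for sizes 6 and 9, and 3.6% for sizes 3, 6 and 9. For 3, 6 and 9 the best guess was still right about 55% of the time. A fixed block of 9 would leave 14.3% certain.

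**The case against.** The strongest objection is that 20% depends on something the article does not say. It requires recruiters to know the block composition and every earlier allocation, in randomisation order, before approaching the next patient. The article gives no accrual rate and does not say when the cardiologist or the nutritionist learns an allocation. The visible cues arrive 7 to 13 days after randomisation, and any patient randomised in that gap is approached with incomplete knowledge. This stands: a reader might infer that a fifth of allocations are in fact predictable, and the article does not support that. It supports a range of 0 to 20% that depends on the delay. The objection does not remove the point, because guessing remains better than chance with one or two allocations unknown.

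A reader might also infer that concealment is absent. A condensed article may leave the custody of the list to the full protocol, so its silence is no fault. The point concerns the constant size that the article does state.

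A third tempting inference is that baseline tests, including the preferred exercise stress test, are done with the arm already known. The text mentions randomisation before it describes the baseline visit, but Table 2 gives no order within day -14 and Figure 1 is not available here. This is a possibility only.

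Finally, the size of any harm is not established. As an illustration under assumed figures, three of 16 patients who are each 1 SD worse would move an arm mean by 3/16 = 0.19 SD, while the chance standard error of a difference between two arms of 16 is √(2/16) = 0.35 SD. The main outcomes are laboratory and histological measures read blind, in a stated proof-of-concept study. Regression for confounders is also planned, but it cannot correct for selection on unmeasured features.

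**Conclusion.** The point holds as a conditional weakness of the stated randomisation rule. Up to 9.6 of 48 allocations (20%) are certain, with best-guess accuracy of 56%, if recruiters know all earlier allocations in order. This falls to 1.6 of 48 (3%) and 45% when they are one patient behind, and to none and 41% when they are two behind. The figures assume 2:2:2 blocks and a single unstratified sequence; hidden stratification would make tracking harder. What follows is a risk of selective enrolment or timing. Nothing in the article shows that steering has occurred or that the results are biased.

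**What to change.** For patients still to be enrolled, generate the remaining list with randomly varying block sizes, for example 3, 6 and 9, and do not disclose the sizes to those who recruit. Under full knowledge of past allocations and of the menu of sizes, this cuts certain allocations from 20% to about 4%. Best-guess accuracy stays near 55% in that case, so varying the sizes is not enough alone, and keeping them undisclosed matters.

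Also state that the allocation is released only after the day -14 baseline measurements are complete. The present schedule allows this, since the first arm-specific step is on day -7, and it settles the order that Table 2 leaves open.

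The cost is a new list and a short amendment. If enrolment stops at 48 within a block of 6 or 9, final arm sizes may differ from 16 by one or two.

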### Setting

Figure 1 depicts a flow chart of the study protocol. The study is currently performed at the department of cardio-thoracic surgery of the AMC. Patients are informed about the study by a cardiologist and nutritionist who hand over the information letter as well as the informed consent form. A patient is included in the study when the informed consent form is signed. Subsequently, the patient can be randomized to one of the three groups: the "enteral group" (n = 16), the "parenteral group" (n = 16), or the control group (n = 16). During visits at the hospital outpatient clinic (approximately two weeks before surgery), patients are subjected to baseline measurements including blood sampling, measurement of body weight and height, bioelectrical impedance spectrometry (BIS), ECG-gated myocardial perfusion scintigraphy (MPS) and a ^18^F-fluorodeoxy-glucose positron emission tomography (^18^F-FDG PET) scan (Table 2). As part of the preoperative evaluation, patients will also undergo preoperative assessments by a cardiothoracic surgeon and an anesthesiologist.

**Figure 1 F1:**
[figure not shown]
**Flow chart of study protocol**. BIS, bioelectrical impedance spectrometry; CABG, coronary artery bypass grafting; ^18^F-FDG PET, ^18^F-fluorodeoxy-glucose positron emission tomography; MPS, myocardial perfusion scintigraphy.

**Table 2 T2:** Study schedule

Days	Before								CABG			After			
	**-14**	**-7**	**-6**	**-5**	**-4**	**-3**	**-2**	**-1**	**0 ** **before**	**0 ** **start**	**0 ** **end**	**1**	**2**	**3**	**>21**

Informed consent	E,P,C														
Randomization	E,P,C														
Blood sampling	E,P,C								E,P,C	E,P,C	E,P,C	E,P,C		E,P,C	E,P,C
MPS	E,P,C														E,P,C
^18^F-FDG PET	E,P,C														E,P,C
BIS	E,P,C														E,P,C
Cardiac tissue										E,P,C	E,P,C				
Aortic tissue											E,P,C				
Nutrient drink		E	E	E	E										
Hospital admission						E,P		C							
Nutrition						E,P	E,P	E,P	E,P	E,P	E,P	E,P	E,P		

BIS, bioelectrical impedance spectrometry; C, control group; CABG, coronary artery bypass grafting; E, enteral group; ^18^F-FDG PET, ^18^F-fluorodeoxy-glucose positron emission tomography; MPS, myocardial perfusion scintigraphy; P, parenteral group.

Patients allocated to the enteral and parenteral group will be admitted at the hospital three days before surgery (Table 2). Patients allocated to the control group will be admitted one day before surgery.

Approximately three weeks after surgery patients will visit the outpatient clinic for measurements including blood sampling, measurement of body weight, BIS, MPS and ^18^F-FDG PET. In addition, as part of the routine clinical postoperative care patients will be seen by a cardiothoracic surgeon.

### Nutrition and administering devices

#### Enteral nutrition

During the four days before hospital admission, the enteral group will take 125 ml per day of a nutrient drink (Nutridrink Compact, Nutricia, Zoetermeer, The Netherlands) consisting of proteins, carbohydrates, fats, vitamins and minerals (Table 3). When admitted to the hospital, patients in the enteral group will receive a solution containing amino acids (PeptoPro, DSM, Delft, The Netherlands), carbohydrates (Fantomalt, Nutricia, Zoetermeer, The Netherlands), and vitamins and minerals (Phlexy-Vits, SHS International Ltd., Liverpool, United Kingdom) which will be prepared at the hospital each day. An amount of 1050 ml of the enteral nutrition will be given during 24 hours. This nutrition will be given two days before, during and two days after CABG by a computerized guidance system-placed nasoduodenal tube (Cortrak^®^, Viasys Healthcare, Wheeling, IL, USA). At the morning of surgery the position of the duodenal tube is verified. Patients are permitted to eat and drink in addition to their supplemental nutrition.

**Table 3 T3:** Composition of enteral and parenteral nutrition

	Enteral group		Parenteral group
	Drink (at home) per day	Nutrition (at hospital) per day	Nutrition (at hospital) per day
Volume (ml)	125	1050	1250
Amino acids (g)	12	80.5	40
Carbohydrates (g)	37.1	95	80
Fat (g)	11.6	1.5	50
Energy (kcal)	300	745	955
Vitamins and minerals	Yes	Yes	Yes

#### Parenteral nutrition

Patients in the parenteral group will receive 1250 ml of nutrition (Nutriflex Lipid peri, B.Braun, Oss, The Netherlands) containing amino acids, lipids and glucose. An amount of 1250 ml of the amino acid infusion (840 mOsm/L) will be given in 24 hours for 5 days (Table 3). In addition, vitamins (Cernevit, Baxter, Utrecht, The Netherlands) and trace elements (Nutritrace, B.Braun, Oss, The Netherlands) will be added to the parenteral nutrition. This nutrition will be given two days before, during and two days after CABG. Patients are permitted to eat and drink in addition to their supplemental nutrition.

#### Controls

The control group follows the standard protocol of the department of cardio-thoracic surgery of the AMC allowing patients to eat and drink until six hours before surgery. The day after surgery, this standard protocol prescribes a (clear) liquid diet. On the second day after surgery patients are recommended a normal diet.

### Outcome measures

The main study outcomes are amino acid profile and cardiomyocytes structure at the time of cardiac surgery. Amino acid profile will be studied in blood plasma and cardiac tissue and includes determining the concentrations of all amino acids, ADMA and symmetric dimethylarginine (SDMA, ADMA's isomer that lacks direct NOS inhibitory activity). In addition, the arginine/ADMA ratio (an indicator of potential NO production) will be calculated. In cardiac tissue, also the activity of dimethylarginine dimethylaminohydrolase (DDAH, an enzyme which degrades ADMA) and arginase (an enzyme which metabolizes arginine) are measured. Cardiomyocytes structure will be assessed by histological analysis, immuno-histochemistry, and by electron microscopy.

The secondary study outcomes are cardiac perfusion, left ventricular function and cardiac glucose metabolism. ECG-gated MPS will be used for the measurement of cardiac perfusion and left ventricular function. Cardiac glucose metabolism will be measured with ^18^F-FDG PET.

BIS measured FFM will be used as parameter of nutritional status. A high FFM is related to better nutritional status and improved post-surgical outcome [9]. Other outcome parameters are cardiac muscle damage and signs of failure as measured by blood plasma biomarkers (Troponin T, CK-MB, and NT-proBNP). Blood plasma will be stored for future study of metabolic switch biomarkers. Baseline characteristics (including European System for Cardiac Operation Risk Evaluation score (EuroSCORE) [10], and unintended weight loss) will be recorded, as well as clinical parameters (intensive care unit (ICU) stay, length of hospital stay, time of mechanical ventilation, organ failure, infections, bleeding, and postoperative mortality). Finally, the concentration of ADMA will be measured in a sample of the aortic wall to investigate the relation between tissue ADMA concentrations in the aorta, and both intracellular concentrations from peripheral blood mononuclear cells (PBMC) and plasma levels.

### Blood and tissue samples

Blood sampling will be done at baseline (approximately two weeks before CABG during a visit at the hospital outpatient clinic), at the day of surgery (once before and twice during surgery), at the first and third day after surgery, and approximately three weeks after surgery (during a visit at the hospital outpatient clinic) (Table 2).

During surgery, two tissue samples of the appendix of the right atrium will be taken by the surgeon. One sample will be taken prior to the start of the anastomosic connection of the bypass graft, and one sample at the end of the procedure before closing of the pericardium. Half of each sample is placed in an aluminum box which will be immediately frozen in liquid nitrogen and stored at -80°C until the amino acid profile is analyzed. The other half of each sample is immediately placed in formalin and will be analyzed within two weeks for the assessment of cardiomyocytes structure. In addition, a sample of aortic tissue is taken by the surgeon at the end of the CABG-procedure which becomes available due to fixation of the proximal anastomosis needed for the bypass and is in routine clinical practice discarded. The sample is immediately frozen in liquid nitrogen and stored at -80°C until the ADMA concentration is measured.

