### Tissue pathological evaluation

The cardiac tissue sample will be fixated in formaline. It then will be studied by histological, immuno-histochemical and ultrastructural analysis. For histological analysis, tissue samples will be stained with hematoxylin and eosin (HE) and Elastica van Gieson (EVG). Subsequently, cardiomyocytes diameter, thickness of the endocardium, level of fibrosis (interstitial, replaced and perivascular) and the percentage of fat tissue contribution (replacement and perivascular) will be analyzed. Periodic acid Schiff digested (PAS/D) stained tissue segments will be evaluated to detect and quantify glycogen stacking. Finally, the presence of iron and amyloid will be established by ferron and Congo-red staining respectively. The immuno-histochemical part of the study includes analysis/quantification of lymphocytes, macrophages, neutrophil granulocytes, myocytolysis, and pro-inflammatory vessel damage by antibodies CD45, CD68, myeloperoxidase (MPO), C3d, and carboxymethyl lysine (CML) respectively. Using electron microscopy, we will determine myofibril density, cytosolic glycogen, expanded sarcoplasmatic reticulum (as marker of cellular damage), amount of mitochondria, damage to mitochondria (stacking as reversible damage, protein dots as irreversible damage), and thickness of the basal membrane of capillaries.

All analysis in this study will be done by analysts that are blinded to group assignment.

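### Electron microscopy belongs to a main outcome, but as written all the tissue it uses is fixed in formalin, which can mimic or mask some of the features scored

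*Protocol article*

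**What the plan says.** The protocol article, under Outcome measures, makes structure a main outcome: "The main study outcomes are amino acid profile and cardiomyocytes structure at the time of cardiac surgery". It names three methods for it: "Cardiomyocytes structure will be assessed by histological analysis, immuno-histochemistry, and by electron microscopy".

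Under Blood and tissue samples, two samples of the right atrial appendage are taken during surgery and each is divided in two. For the amino acid profile, "Half of each sample is placed in an aluminum box which will be immediately frozen in liquid nitrogen". For structure, "The other half of each sample is immediately placed in formalin and will be analyzed within two weeks". No third portion is mentioned.

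Under Tissue pathological evaluation the same route is given again: "The cardiac tissue sample will be fixated in formaline. It then will be studied by histological, immuno-histochemical and ultrastructural analysis". The variables read by electron microscopy are myofibril density, cytosolic glycogen, capillary basal membrane thickness, and this group: "expanded sarcoplasmatic reticulum (as marker of cellular damage), amount of mitochondria, damage to mitochondria". Mitochondrial stacking counts as reversible damage and protein dots as irreversible damage. The same section says that analysts are blinded to group.

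**The concern.** The fixative is chosen at the moment of collection, and the biopsy cannot be repeated. Formalin is the ordinary choice for histology and immunohistochemistry. Electron microscopy usually starts from small pieces put directly into a glutaraldehyde-containing fixative, because formalin alone generally preserves membranes and cytosolic content less well. That is general laboratory method; the documents do not discuss it.

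It matters here because some of the listed variables depend on exactly that preservation. Dilated reticulum is to be read as cell damage, and cytosolic glycogen is to be assessed. If fixation itself widens reticulum or loses glycogen, the reading mixes the patient's state with the handling of the tissue. A finding of no difference could then mean either no effect of nutrition or an insensitive measurement, and the reader could not tell which.

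**Working it through.** **Step 1: trace the tissue from outcome to fixative (all in the protocol article).**

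| Question | Answer | Section |
|---|---|---|
| Is structure a main outcome? | Yes, one of two | Outcome measures |
| Is electron microscopy part of it? | Yes, one of three methods | Outcome measures |
| Where does the first half of each sample go? | Frozen, for the amino acid profile | Blood and tissue samples |
| Where does the second half go? | Formalin, for structure | Blood and tissue samples |
| Which tissue is used for ultrastructure? | The formalin-fixed tissue | Tissue pathological evaluation |

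The two halves account for the whole sample. The last row is stated, not inferred: after the fixation sentence the text continues "It then will be studied by histological, immuno-histochemical and ultrastructural analysis". Number of samples concerned: 48 patients × 2 = up to 96.

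**Step 2: match the risk to the variables.**
- Expanded sarcoplasmic reticulum: overlap with poor membrane preservation is plausible.
- Cytosolic glycogen: loss during fixation is plausible.
- Mitochondrial damage: possible. The protocol scores stacking and protein dots, and nothing in the documents shows that formalin produces either.
- Myofibril density, number of mitochondria, capillary basal membrane thickness: no specific mechanism is established here.
- Histology and immunohistochemistry: not affected by this point.

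**Step 3: direction of the effect.** All three arms follow the same route and the readers are blinded. The artefact is therefore expected to be unrelated to arm, adding noise and not a systematic difference.

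**Step 4: illustration of size.** The document gives no effect size, standard deviation or power for these variables, so there is no figure of its own to reproduce. Assumptions:
- 16 against 16, that is, one nutrition arm against control.
- The unpaired t-test and the 0.05 level from Statistical analysis, taken as two-sided.
- Artefact acting as extra variance, equal in all arms, so that the score has reliability r (true variance divided by total variance).

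Degrees of freedom are 2 × 16 − 2 = 30 and the critical t is 2.042. The noncentrality is d × √(16/2). Power of 80% needs d = 1.024 SD (1.024 × 2.828 = 2.895). With reliability r, the observed standardized difference is d × √r, and the difference detectable with 80% power becomes 1.024/√r in units of the artefact-free SD.

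| Assumed r | 1.024 × √r | Power | 1.024/√r |
|---|---|---|---|
| 1.0 | 1.024 | 80% | 1.02 |
| 0.8 | 0.916 | 71% | 1.14 |
| 0.6 | 0.793 | 58% | 1.32 |
| 0.5 | 0.724 | 51% | 1.45 |
| 0.4 | 0.647 | 43% | 1.62 |

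**Step 5: would dropping the patients already sampled help?** Suppose, for illustration, that half are dropped, leaving 8 against 8 (14 degrees of freedom). Power at 1.024 SD falls to 48% and the difference detectable with 80% power rises to 1.51 SD. That is worse than keeping all patients at a reliability of 0.5 (51% and 1.45 SD).

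**The case against.** The strongest reply is that this is a condensed article. It describes no step of electron-microscopy preparation (no post-fixation, embedding or sectioning), and nobody would conclude that those steps were left out of the study. A laboratory procedure may set aside a separate piece. This has weight for steps on which the article is silent. It does not remove the point, because the primary fixative is stated in two sections and the second says that ultrastructure is read from that tissue. If a separate piece is in fact taken, the two sections misdescribe a main-outcome procedure and need correcting anyway.

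It is also fair to say that the harm falls on one of three methods within one of two main outcomes of a proof-of-concept study. That stands, and limits the weight of the point.

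Three stronger readings are tempting, and the documents do not support them:
- A reader might infer that formalin causes the very changes scored as injury. The documents say nothing about fixation artefact, and for stacking and protein dots the link is not shown. Nor do they support extending the problem to every electron-microscopy variable, or expecting damage scores to reach a ceiling.
- A reader might take the two weeks as time spent in formalin, varying between patients. It is a deadline for analysis; tissue may be transferred or embedded sooner.
- A reader might conclude that patients sampled in formalin only should be left out. That would discard randomized main-outcome data although handling is the same in all arms, and the loss of patients could cost more than the artefact.

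**Conclusion.** The point holds as a risk to measurement quality. As written, the whole structural half of every atrial sample goes into formalin and electron microscopy is done on that tissue. Some of its variables, chiefly reticulum expansion and cytosolic glycogen, and possibly mitochondrial damage, may then be imitated or masked by fixation.

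The consequence is non-differential noise and lost sensitivity, not bias between arms. Its size cannot be derived from the documents. The fall in power from 80% to between 71% and 43% rests wholly on assumed reliabilities of 0.8 to 0.4, a t-test on 16 against 16 and artefact that acts as added variance. The premise about formalin is general laboratory method, not something that the article states. Given how little prevention costs and that the tissue cannot be taken again, the change is worth making.

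**What to change.** In Blood and tissue samples and in Tissue pathological evaluation, state that at collection a small piece (about 1 mm) is cut from the structural half of each atrial sample and placed in a fixative suited to electron microscopy, for example buffered glutaraldehyde or a formaldehyde-glutaraldehyde mix. The rest of that half stays in formalin for histology and immunohistochemistry. If such a piece is already being taken, correct the two sections to say so.

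The article describes the study as under way, so some patients may already have been sampled in formalin only. Keep them in the analysis, record the fixative for every sample, and run a sensitivity analysis by fixative for the electron-microscopy damage scores.

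The cost is one extra vial per sample (up to 96) and slightly less tissue for light microscopy. No further biopsy is needed.
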